### Study interventions

A single ultrasound-guided STB will be administered in the pre-anaesthesia room 1 hour preoperatively. The STB procedure will be performed by a qualified anaesthesiologist under sterile conditions. The patient will be placed in the supine position with the head turned slightly to the contralateral side. A high-frequency linear ultrasound transducer (6–13 MHz) will be positioned in the supraclavicular fossa with a transverse oblique orientation. The brachial plexus will be identified, and the superior trunk (formed by the C5 and C6 nerve roots) will be visualized as a hypoechoic structure lateral to the subclavian artery. A 22-gauge, 50-mm echogenic needle will be inserted using an in-plane approach from lateral to medial, with the needle tip placed adjacent to the superior trunk. Following negative aspiration, the assigned dose of liposomal bupivacaine (66, 44 or 33 mg) will be diluted with normal saline to a total volume of 10 mL and injected in 2–3 mL aliquots under real-time ultrasound guidance to ensure proper spread. Block success will be confirmed 15 min after injection by assessing sensory loss (cold test) and motor weakness (reduced strength of deltoid and biceps muscles) compared with the contralateral side. Following the block procedure, patients will undergo continuous electrocardiogram (ECG) monitoring for 1 hour to enable immediate management of any serious adverse events. Known side effects of STB include nausea, vomiting, constipation, tachycardia, bradycardia, dizziness, headache, somnolence and hypoesthesia. The most serious risk is arrhythmia due to inadvertent intravascular injection, which ultrasound guidance helps to mitigate. Mild adverse events will not require treatment; moderate-to-severe events will receive appropriate pharmacologic intervention. If a severe event occurs after 50% of the dose has been administered, the injection will be discontinued immediately. Acute allergic reactions will be managed according to standard institutional protocols. All adverse events will be fully documented in the case report form.

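### The only stated rule for stopping the injection applies after half the dose is in, so as worded it leaves out severe events in the first 5 of 10 mL

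*Protocol article*

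**What the plan says.** The point lies in the Study interventions section of the protocol article. The assigned dose (66, 44 or 33 mg) is "diluted with normal saline to a total volume of 10 mL and injected in 2–3 mL aliquots under real-time ultrasound guidance", after negative aspiration. On risk, the section states: "The most serious risk is arrhythmia due to inadvertent intravascular injection, which ultrasound guidance helps to mitigate". On stopping, it states: "If a severe event occurs after 50% of the dose has been administered, the injection will be discontinued immediately".

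The other safety sentences in the section deal with different matters:

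- Treatment by severity: "Mild adverse events will not require treatment; moderate-to-severe events will receive appropriate pharmacologic intervention".
- Monitoring: "Following the block procedure, patients will undergo continuous electrocardiogram (ECG) monitoring for 1 hour".
- Allergy: "Acute allergic reactions will be managed according to standard institutional protocols".

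No other section of the article gives a rule for stopping the injection.

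**The concern.** A rule for stopping an injection should apply from the first millilitre. This one adds a second condition to the severe event, namely that half of the dose is already in. A severe event in the first half does not meet it.

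The condition also fits badly with the risk named beside it. Accidental intravascular injection can show itself as soon as drug enters the vessel, and giving the dose in small aliquots lets the operator pause and stop early. A rule that begins only at the halfway mark leaves out that early part. At stake is the wording of a participant-safety instruction. Nothing in the estimation or testing of the trial's endpoints depends on it.

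**Working it through.** **Inputs**, all from the Study interventions section: total volume 10 mL; aliquots of 2–3 mL; doses 66, 44 and 33 mg; threshold 50% of the dose.

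**Volume outside the rule.** Each dose is diluted uniformly, so half the dose is half the volume: 0.5 × 10 mL = 5 mL. The rule as worded covers the last 5 of 10 mL.

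**Dose outside the rule, by group.**

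| Group | Assigned dose | 50% of dose |
|---|---|---|
| A | 66 mg | 33 mg |
| B | 44 mg | 22 mg |
| C | 33 mg | 16.5 mg |

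The threshold is not a fixed exposure. The part left out in Group A (33 mg) equals the whole Group C dose. The article gives no safety reason for tying the rule to a fraction of the assigned dose.

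**Where the mark falls among the aliquots.** The article gives only the range 2–3 mL, so the patterns below are assumptions.

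- 2 mL aliquots: 10 / 2 = 5 aliquots, with breaks at 2, 4, 6 and 8 mL. The 5 mL mark falls inside the third aliquot, and 2 of the 4 breaks (2 and 4 mL) come before it.
- 3 mL aliquots with a remainder: 3 + 3 + 3 + 1 = 10 mL, with breaks at 3, 6 and 9 mL. The mark falls inside the second aliquot, and 1 of the 3 breaks (3 mL) comes before it.

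These counts only illustrate. An immediate stop can be made in mid-aliquot, so the figure that matters is 5 of 10 mL.

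**Does another sentence fill the gap?** Each candidate was read for an instruction to stop.

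| Text | What it governs | Stops the injection? |
|---|---|---|
| Drug treatment of moderate-to-severe events | Treatment, at any dose | No |
| One hour of ECG monitoring | The period after the block, as worded | No |
| Institutional protocols for allergy | Management of allergic reactions | No |
| Aspiration, aliquots, ultrasound guidance | Lowering the chance of an event | No |
| Institutional standard practice for other perioperative care (Randomization and blinding section) | General default for care not spelled out | Not stated |

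None of them says to stop for a severe event in the first half.

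**Could the 50% mark serve another purpose?** One possibility is a minimum dose for the per-protocol set. The Statistical analysis section defines that set only as patients without major protocol deviations and mentions no dose fraction. Another is that the authors meant stopping even when half of the dose is already in; the sentence does not say so.

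**The case against.** The best counter-argument is that the sentence gives one situation in which the injection stops and does not say that it is the only one. The article condenses a full protocol that is not shown, and detailed handling of events during a block could well sit there. Aspiration, small aliquots, real-time ultrasound and a qualified anaesthesiologist all protect from the first millilitre, treatment of moderate-to-severe events is not tied to the dose given, and other care follows institutional practice. On this view the wording is merely unclear, and no patient-level effect can be shown.

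Much of this stands, and it limits the weight of the point. The text never tells the operator to continue, the authors' intent is uncertain, and in practice the operator would very likely stop. But the point does not rest on something left out of a summary. The article prints a safety rule with a limiting condition. Shortening a rule that applied throughout the injection would not introduce a 50% threshold. If the full protocol carries the same condition, it needs the same correction; if it does not, the article misreports it. The safeguards lower the chance of an event but do not say what to do once one occurs.

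**Conclusion.** The concern holds as a fault in the printed wording. Followed literally, the article's only rule for stopping the injection leaves out severe events in the first 5 of 10 mL, although the same section ranks arrhythmia from intravascular injection as the most serious risk. This rests on a direct reading of the text and on uniform dilution; it assumes nothing about event rates.

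The practical effect is probably limited, and the condition is most likely a drafting error. The article gives no rate of severe events during injection, so no number of affected patients is claimed. The co-primary endpoints, power and alpha do not change. The sentence should still be corrected, because a written safety rule should not depend on the operator going beyond it.

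**What to change.** Delete the 50% condition. Suggested wording: if a severe event occurs at any point during the injection, the injection is stopped immediately. The rule then covers all 10 mL instead of the last 5 mL.

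If the 50% mark was meant to define something else, for example who counts as adequately dosed for the per-protocol set, state that separately in the Statistical analysis section. If the full protocol carries the same sentence, correct it there too.

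The cost is an edit to one sentence, best made before recruitment starts (planned June 2026). It needs no extra patients, procedures or data.

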### Primary and secondary outcomes

The co-primary outcomes will be (1) Rest pain NRS score at 48 h post‑surgery; (2) Cumulative opioid consumption within 0–48 h after surgery, converted to oral morphine milligram equivalents (MME). Secondary outcomes will be (1) Rest pain NRS scores at 6 h, 24 h and 72 h post‑surgery; (2) Muscle Balance Scale (MBS) ratings at 6 h, 24 h, 48 h and 72 h; (3) Motor nerve block assessed by the Bromage score at 6 h, 24 h, 48 h and 72 h [23]; (4) American Shoulder and Elbow Surgeons (ASES) functional score at the same intervals (Table 1); (5) Quality of Recovery-15 (QoR-15) score at 24 h and 48 h post‑surgery.

**Table 1. t0001:** The American shoulder and elbow surgeons (ASES) score.

Activity	Unable to do Score = 0	Very difficult to do Score = 1	Somewhat difficult Score = 2	Not difficult Score = 3
Do usual work				
Do usual sport				
Put on a coat				
Sleep on your painful or affected side				
Wash back/do up bra in back				
Manage toileting				
Comb hair				
Reach a high shelf				
Lift 4.5kg above shoulder				
Throw a ball overhand				
Total scores				

A patient-reported subjective rating system was employed to assess the score, comprising two components: pain (50%) and functional capacity (50%), with a total possible score of 100. Higher scores indicate superior shoulder function.

Specific scoring method: pain score = (10-NRS score) *5; Functional score = total score of 10 items *5/3.

ASES score = pain score + function score.

Although liposomal bupivacaine provides analgesia lasting up to 72 h, its most stable and clinically consistent effect occurs within the first 48 h after surgery. This period also represents the critical window for early postoperative rehabilitation, opioid consumption and acute pain control. Therefore, 48 h was selected as the primary time point to capture the most clinically meaningful analgesic difference among groups, while 72 h was retained as a secondary outcome to assess the extended duration of action.

NRS scores range from 0 (no pain) to 10 (worst imaginable pain). Mild pain (1–3) is non‑disruptive to sleep, moderate pain (4–6) mildly disrupts sleep and severe pain (7–9) prevents or awakens from sleep.

The MBS assesses elbow and wrist flexion strength using a 5‑point scale: 0 (no muscle activity), 1 (slight movement), 2 (movement against gravity only), 3 (movement against resistance with reduced strength) and 4 (strong movement against resistance).

The ASES scoring system is utilized to assess the functional performance of the shoulder joint on the affected side (Table 1).

The QoR-15 score assesses the quality of postoperative recovery. It consists of 15 items, each scored from 0 to 10 (0 = completely disagree/very poor condition; 10 = completely agree/excellent condition). The total score ranges from 0 to 150, with higher scores indicating better postoperative recovery quality (Table 2).

**Table 2. t0002:** The quality of recovery-15 (QoR-15) score.

Part	Item no.	Item description	Score (0–10)

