**Methods:**

This randomized, double-blind, controlled trial will enrol 282 adult patients scheduled for elective arthroscopic rotator cuff repair. Patients will be randomly allocated (1:1:1) to receive ultrasound-guided STB with liposomal bupivacaine 66 mg (Group A), 44 mg (Group B) or 33 mg (Group C), each diluted to 10 mL. The co-primary outcomes are (1) rest pain Numeric Rating Scale (NRS) score at 48 h post-surgery and (2) cumulative oral morphine milligram equivalents (MME) consumption within 0–48 h after surgery. Secondary outcomes include rest pain NRS scores at 6, 24 and 72 h; motor function assessed by Muscle Balance Scale, Bromage score and American Shoulder and Elbow Surgeons (ASES) score at 6, 24, 48 and 72 h; and Quality of Recovery-15 (QoR-15) score at 24 and 48 h.

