In practice, high-concentration liposomal bupivacaine for brachial plexus blocks may cause prolonged motor blockade and potential phrenic nerve involvement, which could hinder early rehabilitation [21]. Although STB has been shown to preserve phrenic nerve function while providing comparable analgesia to interscalene block [20], no study to date has systematically evaluated different concentrations of liposomal bupivacaine specifically for STB. The optimal concentration that balances effective, prolonged analgesia with preserved motor function remains unknown. To address this research gap, this study aims to identify the optimal concentration of liposomal bupivacaine for STB in arthroscopic shoulder surgery, seeking to achieve effective and long-lasting analgesia while preserving shoulder joint mobility.

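### Half of the ASES total is rescaled NRS pain, so an unchanged or better total cannot be read as preserved shoulder function; the ten-item function sub-score should be the functional secondary outcome

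*Protocol article*

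**What the plan says.** The Methods paragraph of the Abstract lists, among the secondary outcomes, "motor function assessed by Muscle Balance Scale, Bromage score and American Shoulder and Elbow Surgeons (ASES) score" at 6, 24, 48 and 72 h. The section Primary and secondary outcomes lists the "American Shoulder and Elbow Surgeons (ASES) functional score at the same intervals", separately from MBS and Bromage. The text after Table 1 describes the score as "comprising two components: pain (50%) and functional capacity (50%), with a total possible score of 100". It gives the components as "pain score = (10-NRS score) *5; Functional score = total score of 10 items *5/3" and the sum as "ASES score = pain score + function score", and adds: "Higher scores indicate superior shoulder function". The next part of that section says that ASES measures how the affected shoulder performs.

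The outcome as defined is the total. The function half is an intermediate step in the formula and is not named as an outcome. One co-primary is the "rest pain Numeric Rating Scale (NRS) score at 48 h post-surgery"; rest NRS at 6, 24 and 72 h is secondary.

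The Introduction gives the aim as "seeking to achieve effective and long-lasting analgesia while preserving shoulder joint mobility".

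**The concern.** The trial weighs analgesia against motor preservation, and its own premises have the two moving in opposite directions with dose. Sample size estimation assumes moderate-to-severe pain at 48 h in 15%, 25% and 35% of patients at 66, 44 and 33 mg. The Introduction warns that high concentrations may produce long-lasting motor block. A total that adds a pain term to a function term puts the expected benefit and the expected harm into one number, and the protocol then labels that number function.

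Two consequences follow. Arms with identical function but different pain will differ on ASES. Arms with different function can look alike on ASES, or appear in the wrong order, if the arm with worse function has less pain. This bears on the stated aim because ASES is the only outcome the document describes as shoulder function: MBS is described as grading elbow and wrist flexion, and Bromage is described only as a measure of motor nerve block.

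**Working it through.** **Inputs from Primary and secondary outcomes and Table 1.** NRS 0–10; ten items scored 0–3, so an item total of 0–30; pain part = (10 − NRS) × 5; function part = item total × 5/3.

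**Step 1: reproduce the stated scale.** Maximum pain part: (10 − 0) × 5 = 50. Maximum function part: 30 × 5/3 = 50. Sum 100; minimum 0. The stated 50/50 split and maximum of 100 are correct.

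**Step 2: exchange rate.** One NRS point moves the total by 5. One item point moves it by 5/3. So one NRS point equals 5 ÷ (5/3) = 3 item points, which is 10% of the function range.

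**Step 3: pairs of patients.**

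| NRS | Items | Pain part | Function part | Total |
|---|---|---|---|---|
| 2 | 9/30 | 40 | 15 | 55.0 |
| 4 | 15/30 | 30 | 25 | 55.0 |
| 1 | 0/30 | 45 | 0 | 45.0 |
| 4 | 8/30 | 30 | 13.3 | 43.3 |

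The first two patients tie although one has 6 fewer item points. The third can do none of the listed activities and still scores above the fourth.

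**Step 4: which NRS enters.** The formula does not say rest pain, but no other postoperative NRS is defined or scheduled as an outcome (Table 3). On that reading, only the 48 h ASES contains the co-primary value; the 6, 24 and 72 h scores contain secondary NRS values.

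**Step 5: how large an NRS difference the plan implies.** The protocol gives no mean NRS. If scores were normal with a common SD, 15% versus 35% above a cut-off is a shift of 0.65 SD, and 15% versus 25% is 0.36 SD. For an assumed SD of 1.5 to 2.5, this is about 1.0–1.6 points for 66 versus 33 mg and 0.5–0.9 points for 66 versus 44 mg. At 5 ASES points each, the pain term alone would add about 5–8 and 2.5–4.5 ASES points with no difference in function.

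**Step 6: illustration of masking.** Assumptions, none from the protocol except n: 84 per group (Sample size estimation), true loss of 4 of 30 item points at the higher dose (4 × 5/3 = 6.67 ASES points), NRS SD 2, item SD 4 or 6, no correlation between NRS and items, unadjusted two-sided 0.05. SD of the total = √[(5 × 2)² + (5/3 × item SD)²] = 12.0 or 14.1.

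| NRS benefit at higher dose | Net ASES loss | Power, total (item SD 4 / 6) |
|---|---|---|
| 0 | 6.67 | 0.95 / 0.86 |
| 0.5 | 6.67 − 2.5 = 4.17 | 0.61 / 0.48 |
| 1 | 6.67 − 5 = 1.67 | 0.14 / 0.12 |
| 1.5 | 6.67 − 7.5 = −0.83 | sign reversed |

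Under the same assumptions the function sub-score alone has power above 0.99 (item SD 4) or 0.99 (item SD 6).

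**Step 7: share of variance.** With NRS SD 1.5–2.5 and item SD 2–6, uncorrelated, the NRS supplies 36% to 93% of the variance of the total. The share is largest when item scores vary little.

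**The case against.** A reader might infer that the trial as a whole could miss motor loss at the higher dose. The documents do not support that. MBS and Bromage are separate secondary outcomes at the same four times, and neither is described with a pain term. The superior trunk is formed by C5 and C6, and Study interventions confirms the block by deltoid and biceps weakness, so elbow flexion on the MBS tests the blocked territory. A reader might also infer that every ASES score contains the co-primary; only the 48 h score does. Nor does a 2-point NRS benefit cancelling 6 item points describe an effect the plan assumes: it is arithmetic, and it exceeds the differences in step 5.

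Other objections carry some weight:

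- The motor-function label appears only in the Abstract's compressed list; the body calls ASES functional. That is fair, but the body also reads a higher total as better shoulder function, so the point does not depend on the Abstract.
- The formula is disclosed and linear, so a reader could recover the mean function difference from the ASES and NRS differences. This gives a point estimate but not its confidence interval.
- An analysis plan that is not shown may tabulate the components. It may, but the outcome and its interpretation are fixed in the protocol.
- Nothing decisive rests on ASES. The success rule uses only the two co-primaries, and no sample size depends on it. This limits the severity.
- The sub-score is not free of pain: one item concerns sleeping on the painful or affected side, and others may be limited by pain. The zero-correlation assumption in step 6 is therefore optimistic. Items on sport, lifting and throwing may also sit near zero within 72 h, which would limit the sub-score but would also leave the total mostly pain.

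**Conclusion.** The point holds for ASES and no further. The exchange rate of 5 ASES points, or 3 of 30 item points, per NRS point follows exactly from the published formula. With the protocol's expectation of less pain and possibly more motor block at the higher dose, it means that an unchanged or improved total is not evidence of preserved shoulder function.

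How much masking would occur is not known. The 1.0–1.6 point NRS difference rests on assumed normality and SDs, and the power figures rest on an assumed 4-point item loss, assumed SDs and no correlation. They show that an NRS benefit of about 1 point is enough to matter under plausible values; they do not predict the trial's result. The instrument itself is not at fault. The weakness is using its total as a functional outcome when the randomised factor is analgesic dose.

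**What to change.** Pre-specify the ASES function sub-score (ten-item total × 5/3, range 0–50) at 6, 24, 48 and 72 h as the functional secondary outcome. Report the 0–100 total alongside it for comparison with other studies. State that conclusions about preserved motor function will rest on MBS, Bromage and the function sub-score, not on the total, and bring the Abstract's label for ASES into line with this.

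The cost is one extra or reworded secondary analysis. The items are already collected and the sub-score is already calculated, so no visit, patient or data field is added. The sub-score may still carry some pain influence and may show floor effects early after surgery; both should be acknowledged when it is reported. Making the change before unblinding avoids a post hoc choice between total and sub-score.

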**A. How have you felt in the past 24/48 hours?**			
A1	1	Breathing easily	
A2	2	Good appetite	
A3	3	Feeling energetic	
A4	4	Good sleep quality	
A5	5	Being able to perform personal hygiene and toileting independently	
A6	6	Being able to communicate with family or friends	
A7	7	Receiving support from doctors and nurses	
A8	8	Being able to return to work or perform routine household tasks	
A9	9	Feeling comfortable and in control of emotions	
A10	10	Feeling generally better	
**B. Have you experienced any of the following in the past 24/48 hours?**			
B1	11	Moderate pain	
B2	12	Severe pain	
B3	13	Nausea or vomiting	
B4	14	Feeling worried or anxious	
B5	15	Feeling sad or depressed	
Total		**Sum of all items (0–150)**	

### Data collection

Table 3 outlines the schedule of enrolment, interventions and data measurements in accordance with the SPIRIT guidelines. Demographic data, ASA status, comorbidities, preoperative medications and the age-adjusted Charlson Comorbidity Index (aCCI) are scheduled to be collected prior to anaesthesia. Surgical, anaesthesia and perioperative data, including hemodynamic events, will be documented *via* an electronic system.

**Table 3. t0003:** Schedule of patient enrolment, study interventions, and outcome assessment according to SPIRIT statement.

			Study period				
Timepoint	Enrollment Preoperative visit	Allocation Before surgery	Post-allocation				
			Pre-anesthesia room	6 h	24 h	48 h	72 h
Enrollment							
Inclusion criteria	×						
Exclusion criteria	×						
Written informed consent	×						
Baseline data	×						
Randomization		×					
Allocation		×					
Study interventions							
Group A			**×**				
Group B			**×**				
Group C			**×**				
Outcome assesment							
NRS score				**×**	**×**	**×**	**×**
MME						**×**	
MBS score				**×**	**×**	**×**	**×**
Bromage score				**×**	**×**	**×**	**×**
ASES score				**×**	**×**	**×**	**×**
QoR-15 score					**×**	**×**	

To minimize reporting errors in the study, only investigators who will be blinded to the study design and group assignment will conduct the postoperative follow-up, which will include assessments of postoperative pain and motor block. Outcome measures will be documented and evaluated in accordance with the procedures outlined in the blinded section. An independent Data Monitoring Committee (DMC), composed of an attending orthopaedic surgeon, an attending anaesthesiologist, a pharmacist and a statistician, will oversee the conduct of the study.

